### Trial design

This study will investigate the use of one form of exergames called IMT, and how this compares to usual care of elderly people 70+. The trial will consist of two groups, one for training with the IMT and one group for usual care that will receive the care provided to non-patients elderly, which at this moment is no additional treatment other than recommendations.

The study will be a single blinded, randomized controlled trial. The study will be funded by the patient@home project, and equipment by Entertainment Robotics. Concealed allocation and intention-to-treat analysis will be used. Measurements will be taken at baseline and after intervention. Upon acceptance the protocol will be registered in clinicaltrials.gov.

Potential participants will be interviewed either by the primary investigator or student assistants at Center for Playware, and assessed for inclusion and exclusion criteria. After interviews the primary investigator will enroll participants. After pre-testing, the participants will be randomized and allocated to either control or intervention group (ratio 1:1) by an individual who is not involved in any of the other parts of the study. The randomization sequence will be created using the online platform www.randomization.com. Allocation will be done after pre-testing, as we have earlier experienced that some potential participants dropped out of the study just before starting.

The pre- and post-test will be done by an external physiotherapist blinded to the participants group allocation. The blinding will be done by using participation numbers and pre- and post-data will be obtained on different data-sheets. Participants, supervisors and care givers will not be blinded.

The trial’s results will be reported using domains and categories described in the taxonomy developed by the Prevention of Falls Network Europe, to allow future synthesis of evidence, or study replication [13].

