### Sample size/power analysis

The data from the pilot study (described in Lund and Jessen [11]) was used to do a power calculation. The results showed that for a power of 80 there is a need for 20 persons in each group. As the population of community-dwelling elderly is expected to exhibit a high variance in functional abilities (higher than the population of the pilot study) we have increased the number of participants to 30 in each group. This also allows for dropouts from the study, which we experienced before initializing the pilot study.

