### Statistical methods

#### Primary outcome analysis

Data will be collected from pre- and post-tests. Data will be analyzed for statistically significant differences by first checking that there is a Gaussian distribution and the using paired *t*-test, otherwise using Wilcoxon signed-rank test. The Wilcoxon Signed-Rank Test is selected because the population of community-dwelling elderly is expected to exhibit a high variance in functional abilities. Therefore a normal distribution of the population’s test scores cannot be assumed. The Wilcoxon Signed-Rank Test is a statistical hypothesis test suitable under such circumstances.

“Intention to treat” analysis will be done. These two conditions (ie, all participants, as randomized) are widely recommended as the preferred analysis strategy.

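### The article promises analysis of all participants as randomised, but its paired tests need a post-test from each person and it gives no rule for those without one

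*Protocol article*

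**What the plan says.** - **Population.** The Trial design section states: "Concealed allocation and intention-to-treat analysis will be used". The abstract repeats the promise. The Primary outcome analysis section spells out its meaning: "These two conditions (ie, all participants, as randomized) are widely recommended as the preferred analysis strategy".
- **Tests.** The same section analyses the pre- and post-tests with a paired t-test if the data look Gaussian, "otherwise using Wilcoxon signed-rank test".
- **Measurement times.** Trial design gives two: "Measurements will be taken at baseline and after intervention".
- **Order of events.** Trial design also says: "Allocation will be done after pre-testing, as we have earlier experienced that some potential participants dropped out of the study just before starting". Every randomised person should therefore have a pre-test, and only the post-test can be lost after randomisation.
- **Dropout.** The Sample size/power analysis section says of the increase to 30 per group: "This also allows for dropouts from the study, which we experienced before initializing the pilot study". No rate is given.
- **Other analyses.** The Secondary outcome analysis section closes by saying that no further analyses are planned.

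**The concern.** Both named tests work on a within-person difference between post-test and pre-test. Someone without a post-test has no difference and cannot enter either test unless a value is supplied. The article names the population and the tests, but nothing that connects them for people who miss the post-test. Followed as written, the plan would give a complete-pairs result reported as intention to treat.

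This matters if the people who miss the post-test differ from those who attend. The Discussion says that most participants have balance problems that keep them from reaching a training facility unaided, so loss related to decline or illness is plausible. In the tile arm, loss could also follow from disliking or not tolerating the training. A reader who trusts the intention-to-treat label would not know that such people had left the comparison.

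**Working it through.** **1. The plan's own figure.** The sample size section states: "The results showed that for a power of 80 there is a need for 20 persons in each group", and then "we have increased the number of participants to 30 in each group". The 20 cannot be reproduced, because alpha, sidedness, endpoint, effect, SD and test are not given. If alpha is 0.05 two-sided and power 80%, then by the normal approximation:

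- two-sample: d = (1.960 + 0.842) × √(2/20) = 0.89
- paired: dz = (1.960 + 0.842) / √20 = 0.63

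Both are possible, so the figure is neither confirmed nor refuted. The point does not depend on it.

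**2. Room for dropout.** 20 / (1 − 1/3) = 30, so the increase covers up to one third lost if the variance does not rise. The article gives higher variance as the main reason for the increase, so the real allowance for dropout is not known.

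**3. Who would be analysed.** The dropout rates below are assumed, equal in both arms:

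| Dropout | Complete pairs out of 60 |
|---|---|
| 10% | 60 × 0.90 = 54 |
| 20% | 60 × 0.80 = 48 |
| 30% | 60 × 0.70 = 42 |

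**4. Bias in one arm's mean change.** Let f be the fraction lost, μc the mean change of completers and μd that of dropouts. The arm's full mean is (1 − f)μc + fμd, so completers differ from it by f(μc − μd). With assumed values:

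- 20% lost, dropouts 0.5 SD worse: 0.20 × 0.5 = 0.10 SD
- 30% lost, dropouts 1 SD worse: 0.30 × 1.0 = 0.30 SD

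**5. Bias between arms.** This is the tile-arm term minus the control-arm term.

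- Loss in the tile arm only: +0.10 to +0.30 SD, favouring the tiles.
- Loss in the control arm only: −0.10 to −0.30 SD, against the tiles.
- The same loss in both arms: for example 0.10 − 0.10 = 0.

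If the paired tests are run within each arm, as their form suggests, this cancelling does not help the tile-arm result taken alone.

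**6. Scale.** For a two-sample comparison with 30 per arm, two-sided alpha 0.05 and 80% power, the detectable difference is 2.802 × √(2/30) = 0.72 SD (normal), or 0.74 SD with the t distribution. Then 0.10/0.74 is about 14% and 0.30/0.74 about 41%. This benchmark is for a between-arm test, not for the paired tests named.

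**7. Does the handling rule matter?** In 20,000 simulated two-arm trials with d = 0.886 and equal random dropout, completers only were compared with baseline carried forward (used only as an illustration):

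| Dropout | Power, completers | Power, carried forward | Mean difference, carried forward |
|---|---|---|---|
| 10% | 0.89 | 0.88 | 0.79 |
| 20% | 0.86 | 0.85 | 0.71 |
| 30% | 0.79 | 0.78 | 0.62 |

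The rule barely changes power. It does change who is analysed and what effect is estimated.

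**The case against.** The best defence is that this is an unwritten missing-data rule, not an error. Such rules are commonly left to a statistical analysis plan or full protocol, and neither is shown. Everyone randomised should have a pre-test, so an imputed post-test would let the same paired tests use all 60. The promise can also be read in its ordinary sense: people are analysed in their allocated arm whatever their adherence, and nothing limits post-testing to those still training.

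Much of this stands. A reader might infer that the plan silently drops people without a post-test, or that its tests could never include them. The article does not say the first, and imputation shows the second to be wrong. A reader might also infer that the result would favour the tiles. The documents do not support that: it needs loss concentrated in the tile arm, and decliners lost from the control arm would push the other way. The dropouts actually reported occurred before the pilot began or just before starting, so they say little about loss after randomisation.

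The defence does not remove the conflict. The article's wording has two conditions, and one of them is that all participants are included. It also fixes the tests and closes the list of analyses, so two stated rules do not meet without a third that is not stated.

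One objection concerns the remedy. With a single post-test, a baseline-constrained mixed model gives nearly the same arm effect as a baseline-adjusted analysis of completers, and it does not cure loss driven by unobserved decline. That is correct, and it is why the sensitivity analysis is needed as well.

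**Conclusion.** The concern holds as a mismatch between a promised population and the named tests. With one post-test, expected dropouts, no rule for missing post-tests and no other analysis planned, the tests do not by themselves deliver all participants as randomised.

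The size and direction of any bias are unknown. The range of 0.10 to 0.30 SD in one arm's mean change rests wholly on assumed dropout of 20% to 30% in one arm only, with dropouts 0.5 to 1 SD worse. Similar loss in both arms would largely cancel in a between-arm comparison.

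The Objectives section states a between-group hypothesis, which a paired test does not address. That is a separate matter and lends no weight here, although the change below would also deal with it.

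**What to change.** 1. Replace the paired test as the primary analysis with a between-arm comparison of all randomised participants in their allocated arm, adjusted for the pre-test. ANCOVA or a baseline-constrained mixed model would serve. The mixed model keeps everyone's pre-test; if ANCOVA is chosen, say how missing post-tests enter it. State the assumption that missingness depends only on observed data.
2. Seek a post-test from everyone randomised, whether or not they still train.
3. Add a sensitivity analysis in which missing tile-arm post-tests are set worse, in the direction of poorer performance on each test.
4. Label any paired or complete-pairs result as a completer analysis, not as intention to treat.

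The first step removes bias from dropout that depends on the pre-test. The third shows how far the conclusion could withstand loss that does not. The cost is a change of wording, slightly more analysis work and a few more post-test invitations.

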#### Secondary outcome analysis

Data from the LW test will be calculated in the same way as the primary outcomes.

Adherence will be calculated for the average and standard deviation for the participant. This will be compared to a goal of minimum 90% adherence to training.

Motivation will be based on the average scores and standard deviation from the participant interviews (questionnaire on motivation) as will the acceptability.

There are no other analysis planned for the study.

## Discussion

Investigating if short-term playful training on the IMT will increase mobility, agility, balancing and general fitness of community-dwelling elderly is the goal of the study. A positive result may help creating more training opportunities to help prevent loss of functional capabilities due to inactivity.

The study will bring further insights to if exergames, a field under development with only few RCTs still done, can have a positive effect on the community-dwelling older adults. Further, the IMT will be assessed to see if the way of creating playful experiences as they do is usable in a larger study.

The study has several logistic challenges, as the participants are living at home but most have balancing problems, which prevent them from getting to a training facility on their own. This have been sought dealt with by going into a cooperation with two Danish care-centers, where elderly come one or two times a week to do different activities (arts and social activities mainly). This means that it could be argued that the participants of the study is only a subset of the elderly in general, but this subset is fairly representative for the municipality.
